## Abstract

**Background:**

Severe postoperative pain remains a major problem that is seen in 20 to 40% of patients. The Analgesia/Nociception Index (ANI) is a 0–100 index reflecting the relative parasympathetic activity allowing for intraoperative analgesia monitoring. We have previously shown that an ANI value < 50 immediately before extubation may predict the occurrence of immediate postoperative pain with good performance. We hypothesized that GOAL-Directed ANalgesia may provide reduced immediate postoperative pain and optimized intraoperative remifentanil administration (GOLDAN study).

**Methods:**

The GOALDAN study is an international, multicenter, simple-blind, parallel, prospective, randomized, controlled, two-armed trial. Patients are randomly assigned in a 1:1 ratio in the control group or in the experimental group. Patients will be randomly allocated to either the intervention group (ANI) or the control group (standard care only). In the ANI group, the administration of remifentanil will be goal-directed targeting a 50–80 ANI range, with a prophylactic injection of morphine immediately after extubation if the case of ANI < 50. Our primary objective was to determine whether the prophylactic administration of morphine at the end of the procedure in patients at risk of immediate postoperative pain (ANI < 50 immediately before extubation) could reduce the incidence of the latter by 50% in the post-anesthetic care unit. Our secondary objective was to determine whether the intraoperative use of goal-directed analgesia with an ANI target of 50 to 80 could improve intraoperative hemodynamics and postoperative outcome.

**Discussion:**

Because of the paucity of well-conducted trials, the authors believe that a randomized-controlled trial will improve the evidence for using analgesia monitoring during general anesthesia and strengthen current recommendations for intraoperative analgesia management.

**Trial registration:**

ClinicalTrials.gov NCT03618082. Registered on 7 August 2018

## Administrative information

Note: The numbers in curly brackets in this protocol refer to SPIRIT checklist item numbers. The order of the items has been modified to group similar items (see https://nam12.safelinks.protection.outlook.com/?url=http%3A%2F%2Fwww.equator-network.org%2Freporting-guidelines%2Fspirit-2727-statement-defining-standard-protocol-items-for-clinical-trials%2F&data=04%7C01%7C%7Ccebfabce35fe40e5116c08da0ee97648%7C84df9e7fe9f640afb435aaaaaaaaaaaa%7C1%7C0%7C637838693113378492%7CUnknown%7CTWFpbGZsb3d8eyJWIjoiMC4wLjAwMDAiLCJQIjoiV2luMzIiLCJBTiI6Ik1haWwiLCJXVCI6Mn0%3D%7C3000&sdata=aaHdGNuTEzSHq%2FuqF5QPWlcD%2Fk3o7RX5kAxe%2FUb0WIw%3D&reserved=0).

## Introduction

### Background and rationale {6a}

Severe postoperative pain remains a major problem that is seen in 20 to 40% of patients [1]. Numerous minor or average surgical procedures, some of which are performed by laparoscopy, trigger surprisingly high levels of postoperative pain [1]. To reduce the incidence of severe pain, patients who have undergone surgery, especially procedures deemed to be minor, should be monitored more precisely. Postoperative pain relief should conform to specific procedures and recommendations [2].

Narcosis (loss of consciousness), analgesia, and muscle relaxation are three major components of anesthesia. Unlike the other components, the assessment of analgesia (or “antinociception”), in current clinical practice, is based on clinical signs that are not very specific, such as movement, lacrimation, tachycardia, or hypertension. Optimized analgesia should individualize the nociception/antinociception balance and optimize the prevention of these reactions to surgical stimuli. In recent years, several monitors have been developed to measure the nociception/antinociception balance [3, 4].

Among them, the Analgesia/Nociception Index (ANI) has been developed to assess intraoperative analgesia using variations of the relative parasympathetic tone [5]. The ANI is obtained using the ANI monitor^®^ (MDoloris Medical Systems, Lille, France). This non-invasive device records the ECG tracing from electrodes placed on the patient’s chest and displays an instant (ANIi) and a 2-min moving mean (ANIm) of the ANI. The Calculation of the ANI was previously described in detail [3, 6, 7]. Briefly, the ANI is an index ranging from 0 to 100 derived from the high-frequency component of heart rate variability modulated by the effect of respiration on the RR series representing relative parasympathetic tone, which reflects the nociception/antinociception balance [7, 8]. High ANI values (above 50) indicate predominant parasympathetic tone, as observed in cases of adequate analgesia [8, 9]. In case of nociception, the sympathetic tone increases and the parasympathetic tone decreases, leading to reduced ANI values (below 50) and hemodynamic reactivity [8, 9].

Variations in ANI reflect the changes in nociceptive stimulation during general anesthesia combining various narcotic (propofol, sevoflurane, or desflurane) and analgesic (fentanyl, sufentanil, and remifentanil) agents [5, 10–12]. The target ANI range value during general anesthesia is 50 to 80 in order to optimize the intraoperative administration of opioids, in particular, remifentanil [9].

Given its extremely rapid pharmacokinetic and pharmacodynamic properties (length of time to onset < 1 min and duration of action < 10 min), remifentanil, which has already been used in our earlier ANI studies, appears to be an analgesic agent that is particularly suitable for continuous monitoring of the nociception/antinociception balance [5, 9, 13–15]. However, the use of high doses of remifentanil may lead to the risk of chronic pain, which can be partly prevented by the administration of ketamine, or cause hypotension or intraoperative bradycardia warranting optimization of the intraoperative administration of this drug [16, 17].

In a previous study, we have highlighted the good performance of ANI recorded at the arrival in PACU for the assessment of immediate postoperative pain [14]. The area under the receiver operating characteristics curve (ROC AUC) was 0.86, with 78% sensitivity and 80% specificity to detect patients with moderate to severe pain, assessed with the Numerical Rating Scale (NRS) > 3.

In this study, we used desflurane as an inhaled narcotic agent since it has rapid pharmacokinetics and pharmacodynamics properties because of its low liposolubility [18]. These properties swiftly balance effective concentrations of desflurane during anesthesia and ensure good hemodynamic control and rapid elimination at the end of anesthesia to facilitate early extubation and recovery [18]. The target intraoperative effective expiratory concentration of desflurane can be estimated from the minimum alveolar concentration (MAC) of halogen-based substances [18]. The MAC is defined by the expiratory alveolar concentration of a halogen that reduces movement by 50% in response to a nociceptive stimulus in anesthetized patients. This concentration decreases with age but the age-indexed MAC overcomes this. Overall, a MAC ranging from 0.8 to 1.2 can obtain the same pharmacodynamic objective as a BIS between 40 and 60 (adequate narcosis and reduction in the risk of intraoperative memorization) simply and at lower cost (the use of BIS electrodes is a non-negligible cost in itself) [19, 20]. Conversely, all of the ventilators currently used comprise a gas analyzer and can measure the fraction of halogen agents inspired and expired as well as the MAC without incurring any additional cost.

Following this study showing that ANI could assess NRS > 3 in PACU, we hypothesized that ANI in the end of surgical procedure may also be able to predict immediate postoperative pain. Therefore, we conducted a study showing that after general anesthesia combining desflurane and remifentanil, an ANI value < 50 immediately after extubation predicted the onset of postoperative pain (NRS > 3) in PACU with 86% sensitivity and specificity [15]. This study showed that ANI assessed immediately after extubation exhibits good performance (ROC AUC = 0.89) to predict immediate postoperative pain.

### Objective {7}

Following this study, we hypothesized that immediate postoperative pain in PACU could be reduced in patients with low ANI after extubation using a morphine bolus. Consequently, we designed this controlled, randomized study to establish whether the prophylactic administration of morphine at the end of the procedure in patients at risk of postoperative pain (ANI < 50 immediately before extubation) could reduce the incidence of the latter by 50%. Our secondary objective was to determine whether the intraoperative use of goal-directed analgesia with an ANI target of 50 to 80 could improve intraoperative hemodynamics and postoperative outcome.

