#### Intervention description {11a}

In the control group, patients will receive general anesthesia with propofol, ketamine, and remifentanil (use of neuromuscular blocking agent left to the discretion of the investigator) for induction and desflurane and remifentanil (with or without neuromuscular blocking agent) for maintenance of anesthesia. Anesthetic drug dosing and administration will be left to the discretion of the investigator. Intraoperative Analgesia/Nociception Index (ANI) will be monitored; however, data will not accessible to the investigator but will be stored in the monitor intern memory for further analysis.

In the experimental (ANI) group, patients will receive general anesthesia with propofol, ketamine, and remifentanil (with or without neuromuscular blocking agent) for induction and desflurane and remifentanil for maintenance with a specific algorithm (Fig. 1—study protocol diagram). The administration of remifentanil will be goal-directed by ANI, as well as the prophylactic injection of morphine at the end of surgery.

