#### Sample size {14}

Given the fact that immediate postoperative pain can affect 30% of patients [1], a total of 161 patients per group (322 patients) will give 90% power using a bilateral test with a *p* value of 5% to detect a 50% reduction in the incidence of immediate postoperative pain (NRS ≤ 3) in patients guided by ANI. Given the specific features of this protocol (essentially the direct transfer from operating theater to continuous monitoring or ICU, use of continuous vasopressors), the final decision is to include a total of 380 patients (190 per group). An interim analysis will be scheduled halfway through the enrolment period (95 patients per group). The *p* value used to decide withdrawal from the trial on efficacy grounds is set at 0.003 (correction of the O’Brien-Fleming alpha-spending function).

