## Statistical methods

### Statistical methods for primary and secondary outcomes {20a}

The main analysis will take the form of an intent-to-treat procedure using the Stata^®^ (version 13, StataCorp, College Station) and R (http://cran.r-project.org/) software; all of the statistical tests will be carried out with an α value of 5%. The continuous variables will be presented as mean and standard deviation, provided that distribution is normal (Shapiro-Wilk test, if required). In the event of an anomaly, they will be presented as median, quartiles, and ranges. Qualitative variables will be expressed in numbers and related percentages. Where feasible, graphs will accompany these analyses. Intergroup comparisons will be routinely carried out (1) without adjustment (2) by adjusting factors, the distribution of which might not be balanced between the groups, despite randomization.

The patients will be described and compared between the groups at baseline, according to the following variables: compliance with eligibility criteria, epidemiological characteristics, clinical characteristics, and possible treatments. The initial comparability of both arms will be assessed on the basis of the principal characteristics of participants and potential factors linked to the primary endpoint. Any difference between the two groups in terms of one of these characteristics will be determined based on clinical as opposed to purely statistical considerations. Protocol deviations, patients distributed according to these deviations, and reasons for withdrawal will also be described. The number of patients enrolled and the enrolment graph will be presented per group.

Since a 50% reduction in the incidence of immediate postoperative pain in PACU patients receiving ANI-directed intraoperative analgesia ranging from 50 to 80 must be highlighted, the primary endpoint (percentage of patients with NRS > 3) will be compared using the *x*^2^ paired test or Fisher’s exact test, if applicable.

Secondly, this analysis can be completed in a multivariate situation using a generalized, linear mixed model approach to logistics, considering inter- and intra-site variability. The covariables will be considered in terms of clinical relevance (other treatments, continuous use of vasopressors, type of surgery) and the results of previous univariate analyses. The results will be expressed in terms of related odds ratios and 95% confidence intervals.

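### The stated primary objective (end-of-surgery morphine in patients with ANI < 50) is not what the trial randomises, sizes or tests, so its primary comparison cannot isolate morphine.

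*Protocol article*

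**What the plan says.** All references are to the protocol article.

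- **Objective {7}, and the Methods part of the Abstract.** The primary question is whether "prophylactic administration of morphine at the end of the procedure in patients at risk of postoperative pain" (ANI < 50 just before extubation) halves the incidence of that pain. Steering intraoperative analgesia to an ANI of 50 to 80 is the secondary question, tied to haemodynamics and postoperative outcome.
- **Intervention description {11a}.** The experimental arm gets both parts: "The administration of remifentanil will be goal-directed by ANI, as well as the prophylactic injection of morphine at the end of surgery". Control patients get discretionary dosing. Their ANI is recorded but hidden from the investigator.
- **Sample size {14}.** The premise is that "immediate postoperative pain can affect 30% of patients", and the trial is sized "to detect a 50% reduction in the incidence of immediate postoperative pain" among ANI-guided patients. The pain event is written there as NRS ≤ 3, whereas Outcomes {12} and the statistical methods use NRS > 3.
- **Statistical methods {20a}.** The main analysis is intention-to-treat. The primary test is introduced with "Since a 50% reduction in the incidence of immediate postoperative pain in PACU patients receiving ANI-directed intraoperative analgesia ranging from 50 to 80", so the effect is credited to the component that the objective calls secondary.
- **Additional analyses {20b}.** None are planned.

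**The concern.** The objective, the randomised contrast, the sample size and the primary analysis should all describe one effect. Here the objective names one component in one subset of patients, the design delivers two components to a whole arm, and the analysis section credits the other component.

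What is at stake is what the trial may conclude. Under the objective, a positive result would be reported as evidence for prophylactic morphine. Under the analysis section, the same result would be evidence for ANI-directed intraoperative analgesia. The data would support only the two together, and a null result could not be attributed to either component.

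**Working it through.** **1. What each section fixes**

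| Section | Population | Intervention credited |
|---|---|---|
| Objective {7} | ANI < 50 before extubation | Prophylactic morphine |
| Intervention {11a} | All randomised | Guided remifentanil plus conditional morphine |
| Sample size {14} | Whole ANI arm, 30% to 15% | ANI guidance |
| Statistical methods {20a} | All randomised, intention-to-treat | ANI-directed intraoperative analgesia |

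Two arms that differ in both components cannot separate them. Restricting to ANI < 50 does not rescue the objective. That status is observed after randomisation, and titrating remifentanil to an ANI of 50 to 80 acts on the variable that defines the subset. Flagged patients in the two arms need not be comparable.

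**2. The plan's own figure**

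Inputs: two-sided 5%, 1:1 allocation, 30% versus 15%. The plan states: "a total of 161 patients per group (322 patients) will give 90% power using a bilateral test".

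The pooled-variance formula is n = [1.96·√(2·p̄·(1−p̄)) + 1.2816·√(p₁(1−p₁) + p₂(1−p₂))]² / (p₁−p₂)².

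- p̄ = 0.225; first term 1.96·√0.34875 = 1.157; second term 1.2816·√0.3375 = 0.745.
- n = (1.902)² / 0.0225 = 160.8, so 161 per group. This matches, and power at 161 is 90.0%.

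The stated power is therefore right for the whole-arm contrast.

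**3. Illustration: morphine alone, halving pain only in ANI < 50 patients**

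Background {6a} reports that ANI < 50 predicted NRS > 3 in "PACU with 86% sensitivity and specificity".

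- Flagged: 0.30·0.86 + 0.70·0.14 = 0.356.
- Pain among flagged: 0.258 / 0.356 = 72.5%.
- ANI-arm rate if pain is halved in the flagged only: 0.30 − 0.5·0.258 = 0.171, a 43% relative reduction.
- Power for 30% versus 17.1%: z = (0.129·√161 − 1.96·√0.36008) / √0.35176 = 0.777, so 78.1% at 161 per group. At 190 per group it is 84.5%, if none are lost.
- To reach 15% overall through morphine alone, pain in the flagged would have to fall by 0.15 / 0.258 = 58%.

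This rests on three conditions that the protocol does not state:

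- the 50% applies only within ANI < 50 patients;
- guided remifentanil has no effect on PACU pain;
- the 86% carries over to the trigger. Background {6a} measures it immediately after extubation, whereas Objective {7} sets the trigger immediately before.

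Only sensitivity affects the overall rate. The range is shown below; the 78% is the figure in Background {6a} for ANI at PACU arrival, and the others apart from 86% are assumed.

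| Sensitivity | ANI-arm rate | Power at 161 | Power at 190 |
|---|---|---|---|
| 78% | 18.3% | 69% | 76% |
| 80% | 18.0% | 71.5% | 78.4% |
| 86% | 17.1% | 78.1% | 84.5% |
| 90% | 16.5% | 82.1% | 87.9% |
| 95% | 15.75% | 86.4% | 91.4% |

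**4. Would power be the obstacle within ANI < 50?**

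On the 86%/86% inputs, about 0.356·161 = 57 patients per group are flagged. Comparing 72.5% with 36.2% then has about 98% power. If guided remifentanil halved the number flagged in the ANI arm, power would be 90.8%; if only a quarter remained, 73.2%. Such a comparison could have adequate power and still not be a randomised estimate of the morphine effect.

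**The case against.** The best defence is that the trial itself is coherent. The Abstract's hypothesis is about goal-directed analgesia as a whole, the two-part intervention is disclosed plainly, and the Discussion calls the study pragmatic. Randomised, all-patient intention-to-treat analysis is a valid test of that strategy. The sample size reproduces exactly for the whole-arm target. On this view the objective is loosely worded and nothing in the primary test is biased.

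Most of this stands. The primary test is sound for the strategy. What does not stand is that the wording is harmless: the objective explicitly ranks the morphine question first and guided analgesia second, and the analysis section reverses the credit.

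A reader might also infer that the trial is underpowered for its objective. The documents do not support that. The sample-size and analysis sections apply the 50% to the whole ANI arm, where power is 90%. The 78% figure needs all three conditions listed in the working. The second is fragile: a further relative reduction of (17.1 − 15.0) / 17.1 = 12% from guided remifentanil would restore the planned 15%. The 190 per group is also meant to cover losses, so 84.5% is an upper figure for that scenario.

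The NRS ≤ 3 wording is a separate slip. The endpoint is clear elsewhere and the calculation is unaffected.

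**Conclusion.** The concern holds as a mismatch between the stated primary objective and the trial. The primary comparison estimates the joint effect of guided remifentanil and conditional morphine in all randomised patients. It cannot answer the morphine question, because the components are bundled and because ANI < 50 at extubation is a post-randomisation status. This conclusion needs no numerical assumption, and no sample size would change it.

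Low power is not the reason. At 161 per group the trial has its stated 90% for 30% versus 15%. The fall to about 78% describes one assumed scenario and should not be read as a defect in the calculation.

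**What to change.** 1. In the Abstract and Objective {7}, state the primary objective as the effect of the whole ANI-guided strategy (remifentanil titration plus conditional morphine) versus standard care on NRS > 3 in PACU, in all randomised patients. Drop any claim to isolate morphine.
2. In Statistical methods {20a}, name the same strategy where the primary effect is now credited to intraoperative analgesia alone.
3. In Sample size {14}, change NRS ≤ 3 to NRS > 3. The 161 per group and 90% power stay as they are and match the restated objective.
4. If stored control-arm ANI is ever used to compare ANI < 50 patients, label that analysis exploratory and non-randomised.

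The cost is wording in four places, with no extra patients and no change to procedures or the primary test. The trial gives up a morphine-specific claim that its design could not support.

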### Trial design {8}

The GOALDAN study is an international, multicenter, simple-blind, parallel, prospective, randomized, controlled, two-armed superiority trial. Patients are randomly assigned in a 1:1 ratio in the control group or in the experimental group.

## Methods: participants, interventions, and outcomes

### Study setting {9}

The patients will be recruited from the University Hospital of Clermont-Ferrand, Clermont-Ferrand, France, the Maisonneuve-Rosemont Hospital, Montréal, Québec, and the Pierre Oudot Hospital Centre, Bourgoin-Jallieu, France. Patients will be considered for inclusion if they meet the criteria defined below.

### Eligibility criteria {10}

Participants meeting the following criteria will be included: Adult patients undergoing elective surgery involving general anesthesia with intubation, having an *American Society of Anesthesiologists* (ASA) score of I to III, who have given their consent according to the methods described in article L1122-1-1 of the French Public Health Code, and affiliated to a social security scheme or benefiting from such a scheme.

Participants meeting one or more of the following criteria will be excluded: age under 18 years, elderly patients aged over 75 years [21], general anesthesia without intubation (laryngeal mask), intraoperative local anesthesia with neuraxial block (peridural or spinal block), opioid-free anesthesia, arrhythmia or presence of a pacemaker, outpatient surgery, cardiac or cerebral surgery, obstetric surgery (Cesarean section), surgery performed with local neuraxial or peripheral anesthesia alone, surgery performed in prone position, emergency surgery, endoscopic procedure or interventional radiology, chronic pain treated by opioids, surgery scheduled to take less than 1 h, autonomous nervous system disorder (epilepsy, history of transient ischemic attack or stroke, paraplegia, hemiplegia, orthostatic hypotension, dysautonomia), patient suffering from cardiogenic or septic shock, continuous perfusion of vasoactive agents (ephedrine, phenylephrine, adrenaline or noradrenaline), scheduled postoperative transfer to ICU (patient intubated) after surgery, person under guardianship or curatorship, pregnancy, and breastfeeding.

